### Data collection

The *Growing Together* kit covers the time period from conception until the baby reaches 12 months of age. Thus, we will evaluate the impact of the kit until this time. Outcome data will be collected from women and their partners at the following time points (Fig. 2):2 months postpartum – postal survey with an option of online survey;6 months postpartum – telephone interview;6 months postpartum – partner postal survey with an option of online survey;12 months postpartum – online survey.

**Fig. 2 Fig2:**
[figure not shown]
Data collection processes

#### 2 month survey

After the estimated date of birth of the baby, the hospital’s electronic data system will be checked for the birth outcome, and to ascertain that a live baby is taken home by the mother. Where a baby has died (either in utero or following birth, and prior to discharge from hospital), or where a baby is transferred for ongoing specialist neonatal care, women will be deemed a post randomisation exclusion, and receive no further contact as part of the evaluation. Women who do not continue their pregnancy care at the Women’s, or birth elsewhere will also be considered a post randomisation exclusion.

All remaining eligible women (in both the intervention and standard care arms) will be sent a postal survey when their baby is 2 months of age. A covering letter explaining the evaluation, an 'opt out' form, and two reply paid envelopes will be sent with the survey. The option to opt out will be explained and there will be a separate reply paid envelope in which women can return the form to a hospital midwife to remove their contact details from the survey mail out list. There will also be an option to complete the survey online, with a link included in the cover letter and reminder card. Completion and return of the survey will be considered as informed consent.

The 2 month survey will explore women’s views and experiences of the care and information they received during their pregnancy, birth and postnatal period, as well as their health and emotional wellbeing (Table 1). Women in the intervention arm will also be asked about their views and experiences of the *Growing Together* kit and its usefulness. The 2 month survey will take approximately 20 min to complete.

If women do not return the survey, they will be sent a reminder card 2 weeks later and another copy of the survey 4 weeks after the original survey is sent (if still no response). Women who opt out will not be sent any further reminders and will have no further follow up. Women will be marked as ‘non respondent’ (i.e. lost to this follow-up) if they do not return the survey by the time of data analysis. However, if they do not opt out from the study, they will still be included in the next data collection phase. To assess the mental health of women in the study, returned surveys will be checked for any concerning responses to the EPDS. Women who score high (≥13) or respond positive to the self-harm question will be contacted by an experienced midwife by telephone, as per a protocol to be developed for management of these women.

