**Methods:**

A two-arm cluster randomised controlled trial will be used. Antenatal clinic days will be randomised to either the intervention or standard care arms. Women in the intervention arm receive the kit at their antenatal booking visit. Women in the standard care arm receive the standard information resources at the Women’s. Analyses will be by intention to treat. Inclusion criteria: primiparous women with adequate English-speaking ability and ≤ 30 weeks’ gestation at first pregnancy booking appointment.

The primary outcome of the study is the ‘experience of motherhood questionnaire’ (EMQ), a 20 item validated self-report measure, ranging from 0 to 80, with lower scores indicating better maternal health and wellbeing. To detect a 10% difference in new mothers scoring ≤40 between women who have received the kit (60%) and those who have not (50%), would require 408 per group (total of 816 women) with 95% confidence and 80% power. Allowing for loss to follow up, we aim to recruit 1000 mothers. Secondary outcomes include parents’ views and experiences of their care and of the kit during pregnancy and after the birth, parental attachment, knowledge, confidence, wellbeing and health-seeking behaviour; and emotional, developmental and physical health of the infant. Survey data will be collected from mothers at 2, 6 and 12 months postpartum and partners at 6 months.

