### The ‘parenting kit – Growing Together – at the Women’s hospital

Based on the California kit for New Parents, a parenting kit was developed by the Royal Women’s Hospital (The Women’s) in Melbourne, Australia, a large tertiary referral maternity hospital, to guide prospective and new parents from conception until their child is 1 year of age, titled “*Growing Together*”. Drawing on existing research and the resources already available, *Growing Together* aims to inform parents about the ages and stages of development from conception to 12 months. It provides practical information—from a single authoritative, trusted and non-commercial source—about health care, health promotion, child care and social support and links to Victorian and Australian Government funded parenting services, resources and information.

The Women’s undertook a community engagement process to develop and pilot *Growing Together*, with the aim of then evaluating its impact to determine if a single kit, such as that being developed could meet the needs of all parents.

The content and presentation of the kit was determined in consultation with parents and families; participatory design was integral to its development. Community consultations with a diverse range of families shaped the design and content of the kit, so that messages about the importance of safe and secure relationships, encouraging learning and responding to the individual infant’s personality right from birth are communicated in accessible and empowering ways [17]. There was also a greater focus on parents’ mental health than traditional resources aimed at prospective and new parents. The kit design is generic and not focused only on the Women’s Hospital. Therefore, if it is shown to be acceptable and effective, it could be rolled out more broadly.

There are three parts to the *Growing Together* kit:An A4 size book that covers the journey from conception to 1 year of age.A phone ‘App’ comprising four modules – one each for preconception, pregnancy, parenting, and one for health professionals. The ‘App’ is interactive, and has push notifications, videos and links to various appropriate sites and many other features.A children’s book written by Australian author Mem Fox, titled *Ten Little Fingers and Ten Little Toes,* is aimed at encouraging parents to read to their children, as well as containing what are considered to be important messages for parents.

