### Eligibility criteria and processes

All eligible women booking for pregnancy care at the Women’s during the recruitment period will be included in the study. Inclusion criteria include primiparous women with adequate English-speaking ability (i.e. do not require an interpreter) and at ≤30 weeks gestation at first pregnancy booking appointment. Women will also be included if they had a previous stillbirth and no living children. The rationale for recruiting only primiparous women is that the information needs for first time parents are likely to be different than for parents who have already had a child.

To determine eligibility of women, prior to each randomised clinic day, the project coordinator or PhD student will screen all new booking histories to identify eligible women using the GP referral sheet, or available past history (Fig. 1). If identified as eligible, they are considered to be participants in the trial, in either the standard care or intervention arms as per the clinic randomisation schedule. Details of women who are identified as eligible (in either the intervention or standard care arms) will be entered into a password protected database with their estimated due date. These details will be used to facilitate the later checking of birth outcomes, mail-out of surveys and follow up phone calls at the specified data collection time points (described later). Births will be checked 2 weeks after the due date to ensure, as far as possible, that follow up contact occurs only with women who are discharged home with a live baby. The hospital’s electronic data systems will be used to facilitate this process.

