### Description of standard care

Women in the standard care arm of the trial will receive the standard information resource at the Women’s, a booklet titled ‘*Having your Baby at the Women’s’*. This booklet includes information about care options at the Women’s and services and support provided during pregnancy and birth at the Women’s. It also includes information on how women should take care of themselves during pregnancy, information about different stages of pregnancy and relevant tests and screening as well as information for women to get ready for labour and birth. Care will be delivered in the usual way using standard resources, and these women will be followed up in order to provide a comparison group.

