#### 6 month telephone interview

All eligible women (in both the intervention and standard care arms) will be telephoned by a research midwife when their baby is 6 months of age, to conduct an interview. Women who had previously been excluded or who opted out will not be contacted.

As per Table 1, the 6 month telephone interview will explore: women’s experience of motherhood and caring for their baby; maternal-infant attachment; developmental, emotional and physical health of the baby (including infant feeding and infant temperament – sleeping, crying, settling) and any visits to hospital from birth to 6 months; as well as women’s own wellbeing and health-seeking behaviour since birth. Women in the intervention arm will also be asked about their use of the *Growing Together* kit since birth, and its usefulness. The 6 month telephone interview will take approximately 30 min to complete.

Attempts to contact women will be made as per a structured telephone interview protocol. Where a telephone has been disconnected or a number has changed, the hospital electronic data system will be checked for an updated number. If a woman remains uncontactable by the time her baby is 9 months old (i.e. after 3 months of attempted contact) she will be deemed ‘lost to follow up’ at 6 months. An SMS, asking women to contact us regarding a suitable time for a follow up call, will also be sent 2 to 3 weeks prior to the 9 month cut off as an alternative mode of contact.

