### Data management and analysis

Survey data will be entered into the REDCap data management system [27]. All data will be then transferred to Stata version 14 [28] for data cleaning and analysis.

Data accuracy will be checked through several steps, including verification of the missing data, the range and format of values and checking consistencies and frequency distributions. Any missing or inconsistent values will be checked with the hard copy surveys.

In relation to the trial outcomes, trial arms will be compared using intention to treat analysis. Randomising the various clinic days is likely to result in groups that are evenly distributed - however analyses of study outcomes will be adjusted for baseline differences between the groups as needed. The first stage of the analysis will describe the demographic characteristics in the two trial arms using numbers and percentages, and these data will enable us to understand what factors we need to take into account in the analysis of outcomes. Study outcomes will be compared using χ^2^ and relative risks, with an additional multivariate analysis where there are differences in demographic characteristics of the women in the two trial arms. Comparison of means will be undertaken for continuous variables using t-tests where data are normally distributed or medians compared otherwise using Mann-Whitney U tests.

If the proportions of missing data are above 5%, several steps will be considered to handle missing data. The missing values will be first explored by trial arm and based on the characteristics of the missing data to identify if missing data are missing completely at random (MCAR), missing at random (MAR) or missing not at random (MNAR). Multiple imputation will be conducted considering reasons for and amount of missing data, availability of predictors of missingness and variables that are correlated with the incomplete variable. If the proportions of missing data are very large (more than 40%), only the results of the complete case analysis will be reported and the interpretative limitations of the trial results will be mentioned [29].

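### The analysis is called intention to treat, yet women who leave the hospital's care or birth elsewhere are removed after randomisation

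*Protocol article*

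**What the plan says.** All references are to the protocol article.

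- **Entry to the trial** (Eligibility criteria and processes). Women are screened before each randomised clinic day: "If identified as eligible, they are considered to be participants in the trial, in either the standard care or intervention arms", according to the schedule.
- **Analysis population.** The abstract says "Analyses will be by intention to treat". Data management and analysis says "trial arms will be compared using intention to treat analysis". Neither place qualifies the term.
- **Removal after allocation** (2 month survey). After the due date the hospital's records are checked. Women who have left its care "or birth elsewhere will also be considered a post randomisation exclusion". Loss of the baby before discharge is treated the same way, and "where a baby is transferred for ongoing specialist neonatal care, women will be deemed a post randomisation exclusion".
- **Consequence** (6 month telephone interview). "Women who had previously been excluded or who opted out will not be contacted". Table 1 lists the EMQ at the 6 month interview and at no other time.
- **Missing data** (Data management and analysis). Imputation is planned when more than 5% of data are missing, and complete cases only are reported above 40%. Post-randomisation exclusions are not mentioned.

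**The concern.** Intention to treat means comparing the women as allocated. Here a woman belongs to an arm from screening, receives the kit or the booklet at booking, and can then be removed for something that happens months later. As written she is neither a non-respondent nor lost to follow-up, since the article defines those groups separately. She leaves the trial, and the missing-data plan does not bring her back.

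Two things are at stake. The report would claim a property that the design does not have. And if the arms led different proportions, or different kinds, of women to leave, the groups compared would no longer be those formed by randomising clinic days.

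The point is confined to women who leave care or birth elsewhere. Exclusion after the loss of a baby is a separate matter, since the EMQ would not apply.

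**Working it through.** **1. The plan's own figure.** Inputs from the Sample size section: 50% versus 60% scoring 40 or less, 80% power, 95% confidence (taken as two-sided 5%).

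- Uncorrected: n = [1.96 × √(2 × 0.55 × 0.45) + 0.842 × √(0.25 + 0.24)]² / 0.10², which rounds up to 388 per group.
- With continuity correction: (n/4) × [1 + √(1 + 4/(0.10 n))]², which rounds up to 408 per group, or 816 in total, as stated.

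The sample-size arithmetic is not at fault. The target effect used as the yardstick below is 10 points.

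**2. Order of events.** Screening places the woman in an arm; the kit or booklet is given at booking; she leaves care or births elsewhere; the records check after the due date excludes her; there is no 6 month call and so no EMQ. The excluding event follows both allocation and exposure. This establishes the label problem without any assumed rate.

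**3. Possible bias, with assumed inputs.** The article gives no exclusion rate and no outcome rate for excluded women. Let p be the proportion scoring 40 or less in a full arm, e the proportion excluded, r the rate in retained women and x the rate in excluded women.

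- p = (1 − e) r + e x. With gap g = r − x, this gives r = p + g e.
- If g is the same in both arms, bias = g × (difference in e between arms).
- g = 20 points, equal exclusion: 20 × 0 = 0.
- g = 20 points, 5-point difference: 20 × 0.05 = 1.0 point.
- g = 20 points, 10-point difference: 20 × 0.10 = 2.0 points.

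**4. Variation.** Fix x instead of g, with no true effect and p = 50% in both full arms, using r = (p − e x)/(1 − e):

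| Excluded, kit / standard | x | Retained, kit | Retained, standard | Apparent difference (points) |
|---|---|---|---|---|
| 10% / 10% | 30% | 52.2% | 52.2% | 0 |
| 5% / 10% | 30% | 51.1% | 52.2% | −1.2 |
| 5% / 15% | 30% | 51.1% | 53.5% | −2.5 |
| 10% / 20% | 20% | 53.3% | 57.5% | −4.2 |

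The last row is deliberately severe: its gap between retained and excluded women is 33 to 38 points. The sign reverses if exclusion is higher in the kit arm, or if excluded women score better.

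**The case against.** **There is a reason for the rule.** A reader might infer that excluding women by place of care or birth is arbitrary. The article does not support that. It wants contact only with mothers who took a live baby home, and the check it describes is the hospital's own system. It describes no way of seeing the outcome of a birth elsewhere, so the wish not to contact a bereaved woman plausibly covers these women too. This stands as a reason not to contact them. It is no reason to drop them from the count of women randomised.

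**An effect of the arms on leaving is conjecture.** A reader might also infer that the two packs steer women differently. Of the kit the article says "The kit design is generic and not focused only on" this hospital, and of the standard booklet "This booklet includes information about care options at" this hospital. But the remark on the kit supports a possible wider roll-out, birth care options are one topic among many in its book, and every woman was already booking at this hospital when she received either pack. The rule is also the same in both arms. Nothing shows that leaving differs by arm. If 10% left in one arm (assumed), a 5- to 10-point excess in the other would be a relative rise of 50% to 100%, which is a lot to expect of an information pack.

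**Imputation is weak here.** Some of these women may have had a loss, and an imputed EMQ would then have no meaning. They receive no survey, so few predictors exist beyond referral and booking details. They also never receive the opt-out form. Counting them as missing raises the missing proportion towards the 40% limit above which only complete cases are reported. All of this stands and limits what a sensitivity analysis can show.

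**The rule is open and prespecified.** That is true, and flow reporting by arm may well be in the full protocol. But the article itself fixes both the exclusion and the unqualified label, and the two conflict.

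**Conclusion.** The point holds for the label and the denominator, and this part needs no assumption. Women who belong to an arm are removed for events after allocation and exposure, before the only EMQ assessment, and the comparison of those who remain is called intention to treat.

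It does not extend to a claim that the result will be biased. If exclusion is unrelated to arm, the comparison is unbiased for the retained women, though it answers a question about them only. With an assumed common gap of 20 points and an assumed 5- to 10-point difference in exclusion, the bias is 1 to 2 points against a 10-point target. The harsher assumptions tried reach 4.2 points. Neither the size nor the direction can be derived from the article.

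The plan should be changed, because the label governs what the trial may claim and the change is small. The point does not call the design into question.

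**What to change.** - Keep the no-contact rule as it is.
- Call the primary analysis modified intention to treat wherever the article now says intention to treat, and define it: women with a live baby discharged home, with care and birth at the hospital.
- Keep women who left care or birthed elsewhere in the randomised denominator, as participants with a missing outcome.
- Tabulate exclusions by arm and reason, and compare the arms.
- Add one sensitivity analysis for the missing EMQ of these women, either by imputation from booking data or by varying the assumed proportion scoring 40 or less separately in each arm. The second needs only the counts. State that the analysis applies to women presumed to have a live baby and that few predictors are available. State also whether these women count towards the 40% limit, and confirm that the ethics approval covers analysis of their booking data if imputation is used.

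The cost is some wording, one flow table, one sensitivity analysis and a slightly less favourable label. No further contact with women is needed, and the 408 per group is unchanged.

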#### 6 month telephone interview

All eligible women (in both the intervention and standard care arms) will be telephoned by a research midwife when their baby is 6 months of age, to conduct an interview. Women who had previously been excluded or who opted out will not be contacted.

As per Table 1, the 6 month telephone interview will explore: women’s experience of motherhood and caring for their baby; maternal-infant attachment; developmental, emotional and physical health of the baby (including infant feeding and infant temperament – sleeping, crying, settling) and any visits to hospital from birth to 6 months; as well as women’s own wellbeing and health-seeking behaviour since birth. Women in the intervention arm will also be asked about their use of the *Growing Together* kit since birth, and its usefulness. The 6 month telephone interview will take approximately 30 min to complete.

Attempts to contact women will be made as per a structured telephone interview protocol. Where a telephone has been disconnected or a number has changed, the hospital electronic data system will be checked for an updated number. If a woman remains uncontactable by the time her baby is 9 months old (i.e. after 3 months of attempted contact) she will be deemed ‘lost to follow up’ at 6 months. An SMS, asking women to contact us regarding a suitable time for a follow up call, will also be sent 2 to 3 weeks prior to the 9 month cut off as an alternative mode of contact.

#### 6 month partner survey

A postal survey will be sent (via women) to the partner of all eligible women (in both the intervention and standard care arms) when their baby is 6 months of age. If the survey is not returned, a reminder card will be sent 3 weeks later, and another copy of the survey 5 weeks after the original survey has been sent. The partner survey can also be completed online via a link which will be included in the initial covering letter, reminder card and final reminder letter.

The cover letter will include an option for partners to opt out if they would prefer not to be involved in the study. It will also include a section for women who either never had, or no longer have, a partner to stipulate that they have ‘no partner’. If women have ‘no partner’ or partners opt out, they will be removed from the list of partners for further follow up.

The survey will explore the woman’s partner’s views and experiences of information and care they or their partner received during their partner’s pregnancy and in the period following the birth of their baby (Table 1). They will also be asked about their experience of parenting, caring for their baby, parenting behaviour and paternal-infant interaction as well as about their emotional health and wellbeing. The partner survey will take approximately 10 min to complete.

Similar to the 2 month survey, returned partner surveys will be checked for responses to the EPDS questions and the protocol will be followed if a partner scores high on the EPDS (≥13) or responds positive to the self-harm question.

